## 1 TRIAL SYNOPSIS

|                        |                                                                                                                                                                                                                                                                                                                                                                                                                                                                                                                                                                                                                                                                                                                                                                                                                                                                                                                                                                                                                                                                                                                                                                                                                                                                                                                                                                                                                                      |
|------------------------|--------------------------------------------------------------------------------------------------------------------------------------------------------------------------------------------------------------------------------------------------------------------------------------------------------------------------------------------------------------------------------------------------------------------------------------------------------------------------------------------------------------------------------------------------------------------------------------------------------------------------------------------------------------------------------------------------------------------------------------------------------------------------------------------------------------------------------------------------------------------------------------------------------------------------------------------------------------------------------------------------------------------------------------------------------------------------------------------------------------------------------------------------------------------------------------------------------------------------------------------------------------------------------------------------------------------------------------------------------------------------------------------------------------------------------------|
| Title                  | Adjuvant chemoradiotherapy compared with adjuvant chemotherapy for gastric cancer after D2 gastrectomy: a multicenter phase III randomised controlled trial                                                                                                                                                                                                                                                                                                                                                                                                                                                                                                                                                                                                                                                                                                                                                                                                                                                                                                                                                                                                                                                                                                                                                                                                                                                                          |
| Version number         | V1.4, August 30, 2012                                                                                                                                                                                                                                                                                                                                                                                                                                                                                                                                                                                                                                                                                                                                                                                                                                                                                                                                                                                                                                                                                                                                                                                                                                                                                                                                                                                                                |

| Study Center           | West China Hospital                                                                                                                                                                                                                                                                                                                                                                                                                                                                                                                                                                                                                                                                                                                                                                                                                                                                                                                                                                                                                                                                                                                                                                                                                                                                                                                                                                                                                  |
| Study Design           | Prospective, Randomized, Multicenter, open-label, phase III trial                                                                                                                                                                                                                                                                                                                                                                                                                                                                                                                                                                                                                                                                                                                                                                                                                                                                                                                                                                                                                                                                                                                                                                                                                                                                                                                                                                    |
| Target population      | Gastric carcinoma                                                                                                                                                                                                                                                                                                                                                                                                                                                                                                                                                                                                                                                                                                                                                                                                                                                                                                                                                                                                                                                                                                                                                                                                                                                                                                                                                                                                                    |
| Number of patients     | 620 patients                                                                                                                                                                                                                                                                                                                                                                                                                                                                                                                                                                                                                                                                                                                                                                                                                                                                                                                                                                                                                                                                                                                                                                                                                                                                                                                                                                                                                         |
| Objectives             | Primary Endpoint: Disease-Free Survival (DFS).
Secondary Endpoint: Overall Survival (OS) and treatment-related adverse event.                                                                                                                                                                                                                                                                                                                                                                                                                                                                                                                                                                                                                                                                                                                                                                                                                                                                                                                                                                                                                                                                                                                                                                                                                                                                                                     |
| Inclusion Criteria     | 
(1) Age 18-70 years;
 
(2) Pathologically confirmed gastric cancer patients who have undergone surgical resection;
 
(3) Surgery is radical, achieving R0 resection, and D2 lymph node dissection (with organ preservation) (the number of lymph node dissection should be <math>\geq 15</math>);
 
(4) The time to surgery is not more than 3 months;
 
(5) According to the 2010 edition of UICC/AJCC staging criteria, postoperative pathological stage T stage <math>\geq</math> T4a, N stage <math>\geq</math> N0; and no tumour metastasis or postoperative recurrence is detected by comprehensive examination, i.e., the M stage is M0;
 
(6) Eastern Cooperative Oncology Group (ECOG) performance score: 0-1;
 
(7) Patients who have not received radiotherapy and systemic chemotherapy before or after surgery;
 
(8) Normal function of major organs.
 
(9) Women of childbearing potential must have had a negative pregnancy test (serum or urine) 7 days prior to enrolment and be willing to use an appropriate method of contraception for the duration of the trial and for 8 weeks after the last dose. For males, surgical sterilisation should be applied or agreement to use an appropriate method of contraception for the duration of the trial or 8 weeks after the final dose.
 
(10) Subjects voluntarily enrolled in the study, signed an informed
 |

|                      |                                                                                                                                                                                                                                                                                                                                                                                                                                                                                                                                                                                                                                                                         |
|----------------------|-------------------------------------------------------------------------------------------------------------------------------------------------------------------------------------------------------------------------------------------------------------------------------------------------------------------------------------------------------------------------------------------------------------------------------------------------------------------------------------------------------------------------------------------------------------------------------------------------------------------------------------------------------------------------|
|                      | consent form, were compliant, and cooperated with follow-up visits.                                                                                                                                                                                                                                                                                                                                                                                                                                                                                                                                                                                                     |
| Exclusion Criteria   | 
(1) Previous or concurrent other malignancies, except cured basal cell carcinoma of the skin and carcinoma in situ of the cervix;
 
(2) Pregnant or breastfeeding women;
 
(3) Patients with severe cardiovascular disease and diabetes that cannot be easily controlled;
 
(4) People with mental disorders;
 
(5) People with serious infections;
 
(6) Hypersensitivity to S-1 or platinum oxalate;
 
(7) Serious gastrointestinal diseases that affect the absorption of oral chemotherapeutic drugs
 
(8) Participation in another clinical trial within 4 weeks prior to the start of treatment.
                        |
| Randomization        | Patients were assigned in a 1:1 ratio to SOXRT arm or SOX arm by block randomization.                                                                                                                                                                                                                                                                                                                                                                                                                                                                                                                                                                                   |
| Treatment            | 
This is a multicenter, phase III clinical trial led by West China Hospital, Sichuan University. Patients will be randomly assigned to either the SOXRT arm (experimental group) or the SOX arm (control group).
 
SOXRT arm: Patients will receive one cycle of induction chemotherapy with the SOX regimen 21 days prior to radiotherapy initiation, followed by S-1-based concurrent chemoradiotherapy. After completing radiotherapy, patients will undergo three additional cycles of SOX chemotherapy, with the same dosing regimen as in the induction chemotherapy.
 
SOX arm: Patients will receive a total of six cycles of SOX chemotherapy.
 |
| Statistical Analysis | 
Categorical variables were compared with the use of Chi-squared test or Fisher' s exact test. Kaplan – Meier method was used to analyses the DFS and OS, log-rank test to assess the significance, and Cox proportional hazards model to calculate hazard ratio (HR). The median follow-up time was calculated by reverse-KM method. Statistical significance was defined as a two-side P value < 0.05.
                                                                                                                                                                                                                                                       |

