## 2 Background

Surgery is the primary modality for the treatment of resectable gastric cancer, and radiotherapy can improve local control rates, but does the benefit of local control with postoperative radiotherapy translate into a survival benefit? The landmark INT-0116 study demonstrated that postoperative adjuvant radiotherapy (45 Gy/25 doses) given after radical surgery for gastric cancer increased 3-year survival from 41% to 50% ( $P < 0.001$ ), and the NCCN guidelines recommend postoperative adjuvant radiotherapy for patients with postoperative stage T2N0M0 and above. However, the lack of standardisation of the surgical approach and the fact that D2 resection accounted for only 10% of the patients in this study have led to ongoing controversy. To address this issue, the Korean ARTIST phase III study focused on postoperative D2 patients and showed that concurrent radiotherapy (45 Gy/25 sessions) improved DFS by 5.2% in the lymph node-positive subgroup, although it did not improve overall DFS ( $P=0.0365$ ). This result suggests the need to re-evaluate the precise benefit of radiotherapy in the post-D2 population.

Moreover, our department has previously conducted a phase I/II clinical study of the FOLFOX regimen combined with synchronous radiotherapy (at a dose of 50.4 Gy) after gastric cancer surgery, which confirmed the efficacy and safety of 50.4 Gy of radiotherapy combined with synchronous chemotherapy. The results of the phase II clinical study showed that the 1- and 2-year OS and DFS of the FOLFOX regimen combined with synchronous after radical D2 surgery were 95%, 82% and 85%, 78%. And the phase I/II clinical study of SOX regimen combined with synchronous radiotherapy after gastric cancer has been completed, after which the maximum tolerated dose (maximum tolerated dose, MTD) and safety of S-1 during synchronous radiotherapy have been explored. On this basis, I expect to further develop this multicenter phase III randomized controlled clinical study to explore the value of SOX regimen combined with simultaneous radiotherapy in the adjuvant treatment of gastric cancer patients after D2 radical surgery.

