## 4 Trial design

4.1 Randomisation: patients who met the inclusion criteria and signed the informed consent

were randomly grouped into a synchronous radiotherapy group (experimental group) and a chemotherapy-only group (control group) in a 1:1 ratio.

4.2 The protocol of the experimental group: one cycle of induction chemotherapy (SOX) was administered 21 days before radiotherapy; the specific dosage of SOX was S-1 30-40mg/m^2 bid D1-14, oxaliplatin 130mg/m^2 D1,Q3W, and then S-1 simultaneous radiotherapy was started, and the dosage of S-1 was 50mg bid during the period of simultaneous radiotherapy, which was used in combination with radiotherapy for 5 days a week for a consecutive period. in combination, 5 days per week for 28 days. After 3-4 weeks of radiotherapy, the SOX regimen was administered for 3 cycles at the same dose as the induction chemotherapy.

4.3 Control regimen: A total of 6 cycles of SOX regimen (at the same dose as in the experimental group) will be given.

4.4 Radiotherapy: radiotherapy was started within 3 months after surgery. The radiotherapy dose was 50.4 Gy/28f, 1.8 Gy/d, 5f/w. Radiotherapy was given on the 1st-5th day of each week for 28 consecutive days; radiotherapy was given by three-dimensional conformal radiotherapy (3D-CRT) or intensity-modulated radiotherapy (IMRT).

i. Radiotherapy localisation: fasting for 4 hours before localisation; supine position, hands on elbows, body mould fixation, CT simulation localisation, enhanced scanning, scanning range from T6 lower edge to L4 lower edge, layer thickness 3mm.

ii. Radiotherapy target zone (CTV) reference: postoperative radiotherapy target zone of gastric cancer includes tumour bed, anastomosis and regional lymph nodes. For the specific outlining method of target area, refer to 'Annex 1 Specification for Outlining Target Area of Postoperative Radiotherapy for Gastric Cancer' provided in this protocol.

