# 10 Study assessment

10.1 Effective evaluation indicators: The primary purpose is: DFS. The secondary purpose is: and OS.

10.2 Safety evaluation index: including all toxic side effects and adverse events observed during the trial.

10.3 Sample content estimation: we hypothesised that synchronous radiotherapy would result in higher DFS. with a double significance level of 0.05 and a certainty of 80%. We expect that the 3-year DFS of SOX regimen combined with simultaneous radiotherapy can be at least 8% higher than that of the chemotherapy-only group, i.e., from 70% to 78%. Based on the sample size formula for the comparison of the two sample rates, the sample size needed for this project was calculated to be 516 patients; assuming that 20% of the patients would need to be excluded from the statistics, the total number of patients that would need to be enrolled in this project would be 620.

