## 10.4 Statistical methods

All clinical data were analyzed using IBM SPSS Statistics (IBM Corp., Armonk, NY, USA. version 29.0) and R software (version 4.2.1). Categorical variables were compared with the use of Chi-squared test or Fisher's exact test. Kaplan–Meier method was used to analyses the DFS and OS, log-rank test to assess the significance, and Cox

proportional hazards model to calculate hazard ratio (HR). The median follow-up time was calculated by reverse-KM method. Statistical significance was defined as a two-side P value < 0.05.

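### No stratification factor is named for the blocks, the log-rank test or the Cox model, although nodal status is known for every patient at entry; stratifying the primary DFS analysis on it is a small, free gain

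*Protocol*

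**What the plan says.** - **Randomisation.** The synopsis (Randomization row) reads "Patients were assigned in a 1:1 ratio to SOXRT arm or SOX arm by block randomization". Section 4.1 adds only the split into an experimental group and a "chemotherapy-only group (control group) in a 1:1 ratio". Neither names a stratification factor.
- **Analysis.** Section 10.4, like the synopsis, gives Kaplan–Meier for DFS and OS, "log-rank test to assess the significance", and a Cox model for the hazard ratio. Neither place names strata or covariates.
- **Nodal status at entry.** Inclusion criterion 5 (synopsis and section 5.1) sets eligibility by postoperative pathological T and N stage and admits N0 and above. Criterion 3 asks for at least 15 dissected nodes. Every randomised patient therefore has a recorded N stage, and the population mixes N0 and N+.
- **Background.** Section 2 reports that in an earlier phase III trial after D2 surgery, concurrent radiotherapy "improved DFS by 5.2% in the lymph node-positive subgroup, although it did not improve overall DFS". It then concludes that the benefit needs re-evaluation in the post-D2 population.
- **Planned effect.** Section 10.3 plans for 3-year DFS of 70% versus 78%, two-sided 0.05, 80% power, 516 patients, raised to 620 for exclusions.

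**The concern.** A baseline factor that is likely to be prognostic, is already collected and is cited in the background plays no part in the allocation or analysis as written. If N+ patients relapse faster than N0 patients, this has two consequences.

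First, a plain log-rank test compares arms across a mixture of risks. The unadjusted hazard ratio is then pulled somewhat towards 1 relative to the within-stratum effect, and power is lost. Second, blocks without nodal strata balance total numbers but not nodal status. A chance difference between arms would be left in the primary estimate, and readers of an open-label trial would ask about it.

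At stake is a modest amount of power and the ease of defending the result, not the validity of the test.

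**Working it through.** **1. The plan's own figure.** Inputs from section 10.3: 0.70 versus 0.78, two-sided 0.05, 80% power, two-proportion formula.

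n per arm = [1.960·√(2·0.74·0.26) + 0.842·√(0.70·0.30 + 0.78·0.22)]² / 0.08² = [1.2158 + 0.5199]² / 0.0064 ≈ 471, or 942 in total.

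The stated 516 does not reproduce, and 620 is 516 × 1.2. That is a separate matter. It counts here because it sets the starting power: 54% at 258 per arm and 62% at 310 per arm.

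**2. Effect as a hazard ratio.** Under proportional hazards, ln(0.78)/ln(0.70) = 0.697.

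**3. Assumptions not in the documents.** N+ share π of 70% or 85%; N+ versus N0 hazard ratio ψ of 2, 3 or 5; exponential times; the same treatment hazard ratio of 0.697 in both strata; follow-up of 3 or 5 years per patient. The protocol speaks of 3-year DFS but gives no total follow-up. The N0 hazard λ solves (1−π)·exp(−3λ) + π·exp(−3λψ) = 0.70. For example, π = 0.70 and ψ = 3 give 3-year DFS of 85.8% in N0 and 63.2% in N+.

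**4. Simulated power.** 20,000 trials per scenario, unstratified blocks of 4, both tests on the same data, success at z < −1.96 in favour of radiotherapy. Entries are power in %, plain → stratified log-rank, with the gain in points (rounded after subtraction).

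| Follow-up | N | N+ share | ψ = 2 | ψ = 3 | ψ = 5 |
|---|---|---|---|---|---|
| 3 y | 516 | 70% | 54.1 → 54.7 (0.6) | 53.2 → 55.1 (1.9) | 51.7 → 54.8 (3.1) |
| 3 y | 516 | 85% | 54.0 → 54.5 (0.5) | 54.0 → 54.9 (0.8) | 53.2 → 54.8 (1.6) |
| 3 y | 620 | 70% | 61.6 → 62.6 (1.0) | 61.3 → 63.2 (2.0) | 60.0 → 63.4 (3.4) |
| 3 y | 620 | 85% | 62.5 → 63.1 (0.6) | 61.9 → 63.1 (1.2) | 61.6 → 63.3 (1.6) |
| 5 y | 516 | 70% | 71.4 → 73.0 (1.6) | 68.4 → 72.2 (3.8) | 66.1 → 72.1 (6.0) |
| 5 y | 516 | 85% | 71.8 → 72.6 (0.8) | 71.1 → 72.8 (1.7) | 70.3 → 73.0 (2.7) |
| 5 y | 620 | 70% | 78.9 → 80.3 (1.4) | 76.4 → 79.4 (3.0) | 74.2 → 79.8 (5.6) |
| 5 y | 620 | 85% | 79.7 → 80.4 (0.7) | 78.5 → 80.2 (1.7) | 77.5 → 80.2 (2.8) |

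The standard error of a gain is 0.13 to 0.24 points. In a run of 3,000 trials the largest would be 0.24 × √(20,000/3,000) ≈ 0.6, so a top value anywhere between 6 and 7 is the same result. No scenario shows a loss.

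**5. If the effect were confined to N+.** With marginal 3-year DFS held at 70% and 78% and three years of follow-up, the gain reached 4.2 points at most (63.4% → 67.6%; 620 patients, 70% N+, ψ = 4; 3,000 trials).

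**6. Stratified blocks alone.** In the same set of runs with a common effect, 620 patients and 70% N+, the plain test had power of 63.2% with unstratified and 62.2% with stratified blocks at ψ = 2.5, and 62.7% versus 63.6% at ψ = 4. With a standard error of about 0.9 points, that is no visible gain. The power comes from the stratified test.

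**7. Chance imbalance.** With 310 per arm and 30% N0, the standard deviation of the between-arm difference in nodal share is √(2·0.30·0.70/310) = 3.7 points. A gap of 5 points or more then has probability 2·[1 − Φ(0.05/0.0368)] ≈ 17%. With 15% N0 it is about 8%. At ψ = 3, a 5-point gap moves 3-year DFS by 0.05 × (85.8 − 63.2) ≈ 1.1 points, against a planned difference of 8.

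**The case against.** **Strata may be in an analysis plan that is not shown.** This stands in part. The protocol nowhere calls the log-rank test unstratified or the Cox model unadjusted, and such detail is often left to the analysis plan. A reader should not infer that the sponsor has committed to an unadjusted analysis. Randomisation strata are protocol content, though, since no later document can add them for patients already allocated. A nodal-stratified test is also a concrete improvement on the method as written.

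**The plain test is valid.** This stands in full. After 1:1 randomisation the plain log-rank test controls type I error, and chance imbalance is already part of its sampling error. A reader might infer bias; nothing supports that.

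**Nodal status is not the basis of the trial.** This stands too. Section 2 might be read as saying that benefit was limited to N+ patients, or that the rationale rests on nodal status. It reports a subgroup gain without an overall gain and concludes about the post-D2 population. Section 3 states no nodal hypothesis. Nodal status is a factor that the background cites, no more.

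**The gain rests on assumed values.** Correct. A gain near 6 points needs five-year follow-up, 30% N0 and a prognostic hazard ratio of 5 together, and the protocol states none of these.

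**Conclusion.** The point holds as a free improvement of modest size. No stratification factor is named for the allocation or the DFS analysis, although one suitable factor is on record for every patient. Under the assumptions in step 3, stratifying the test is worth about 0 to 3 points of power at the three-year horizon and about 1 to 6 or 7 points with five years of follow-up. It also answers the question of nodal imbalance in advance.

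It is tempting to read this as a remedy for the trial's low power, and it is not one. At three years the stratified test reaches about 55% with 516 patients and 63% with 620, because the stated inputs call for about 942 evaluable patients. The entries near 80% need all 620 analysed with five years of follow-up each, and there the plain test is already at 74% to 80%. The sample size needs its own correction.

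**What to change.** In section 10.4 (and the synopsis), before any outcome data are seen, state that the primary DFS comparison is a log-rank test stratified by pathological nodal status (N0 versus N+) and that the hazard ratio comes from a Cox model stratified the same way. Keep the unstratified log-rank test and Cox model as a sensitivity analysis. If an analysis plan already says this, make the protocol agree with it. Timing matters: a stratified test adopted after the results are known would look selective.

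State also that the stratified hazard ratio is a within-stratum effect, while the Kaplan–Meier 3-year rates still describe the whole population.

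If enrolment is still open, stratify the blocks by nodal status as well, for balance rather than power.

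The cost is one or two sentences and, if blocks can still be changed, one field on the randomisation form. It needs no new data and no extra patients.
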